### Data management and monitoring

The requirements regarding information in the medical records adhere to the Patient Data Act (SFS 2008:355) and ‘The Medical Product Agency’s regulations on clinical trials of medicinal products for human use’ (LVFS 2011:19). The investigator must keep source documents for each subject in the study. An eCRF is used for data collection. The eCRF is provided in the web-based SAS system PheedIt. This database is provided by Region Stockholm and is registered at CTO, Centre for Clinical Cancer Studies, Cancer Theme, Karolinska University Hospital, Stockholm, Sweden. For details and information that is study specific and of no interest for the medical care of the subject, CRF and other documents may be considered as source data.

Prior to study start the expected source location of source data (eg, medical record, laboratory reports, validated questionnaires and the eCRF), must be identified and documented. This will be done by completing a site-specific source data list. This list defines what documents contain the source data for each study specific parameter. All information processed by the sponsor will be pseudonymized (coded) and study subjects will be identified by a study ID.

A monitor from the CTO at Centre for Clinical Cancer Studies (CKC), Cancer Theme, Karolinska University Hospital will be responsible for coordinating the monitoring activities of the study and ensure adherence to ICH-GCP guidelines. The monitor will have access to medical records and source data after a secrecy agreement has been signed by the responsible party at the site as well as by the monitor. The investigator must ensure that all source documents are accessible for monitoring and other quality control activities.

### Sample size calculation and statistical analyses

The sample size calculation was done assuming a mean difference in log10-transformed AMH-levels of 0.22 between GnRHa group and placebo group (with a ratio 1:1). It was further assumed that data are approximately normally distributed, and that each treatment group has a SD of 0.63.^26^ Under these assumptions, the hypothesis test (a two-sided test with significance level 5%) of the mean effect between GnRHa group versus placebo group will have a power of at least 80% if the sample size is 300 (including an assumed 15% drop-out rate).

Primary and secondary endpoints will be evaluated using the intention-to-treat (ITT) (ie, all randomised subjects), the per protocol (PP) analysis set (ie, all randomised subjects with no major protocol violations) and the safety analysis set (all subjects) (figure 2). The classification of each subject with respect to each analysis set will be done prior to database lock.

**Figure 2 F2:**
[figure not shown]
Study flow chart. GnRHa, gonadotropin-releasing hormone agonists; ITT, intention to treat; PP, per protocol.

Continuous variables will be summarised as number of subjects (n), mean, median, SD, quartile 1 (Q1) and quartile 3 (Q3) and range (min, max) by visit. The change from baseline at each respective visit will also be presented. Discrete (categorical/ordinal) variables will be summarised in frequency tables (frequency and proportion) by visit. All statistical tests will be two-sided assuming a 5% significance level.

Statistical analyses will be performed using SAS (V.9.4 or higher, SAS Institute, Cary, NC, USA) unless otherwise stated.

### Data analysis plan

An interim report will be produced after last enrolled subject has completed follow-up 12 months after EoT (primary endpoint). The interim report will include analyses of the primary and some secondary endpoints based on data assembled for each enrolled subject up until the time point corresponding to 12 months after EoT. The assembled data will be locked and the study unblinded only for the statisticians. Main analysis for the primary endpoint will be done using the ITT population. Analysis on the PP population will be performed as sensitivity analysis. Subgroup analysis will be performed on ITT population for AMH change on these prospectively defined subgroups:

Age (14–19; 20–34; **≥**35)Ovarian reserve (AMH) at baseline (0.68–2.3; 2.4–4.9; **≥**5 (µg/L)).Cancer diagnosis (breast cancer, lymphoma, sarcoma and leukaemia)Type of cancer treatment (high risk, intermediate risk and low risk).Exposure to gonadotoxic cytostatics (corresponding to cumulative dose, mg CPA)/.

Analyses results and aggregated descriptive summaries will be disclosed to the sponsor.

At the end of study, after the extended follow-up period of 5 years, and once all study data for the mentioned visits are collected and verified in the eCRF system, the unblinding of all subjects will take place for investigators and sponsor. All available data will be used in the statistical analysis. A subject who withdraws prior to the last planned visit in the study will be included in the analyses up to the time of discontinuation. All efficacy and safety analyses will be performed at end of study when the study database is released for unblinding.

### Safety and adverse events

The study drug is well established for other indications in Sweden and used off-label for this indication in Sweden and globally. During the study, we will register standard safety blood samples at baseline and at EoT as well as access the safety blood markers taken during chemotherapy through the subject’s medical records. At each study visit, adverse events (AE) related to the study product are registered, starting at study randomisation and up to 90 days after the last dose of the investigational products, triptorelin and placebo (sodium chloride). All AE that occur during the study and which are observed by the investigator/study nurse or reported by the subject will be registered in the eCRF with complete information regarding seriousness (mild, moderate and severe), intensity and causality. Serious adverse events (SAE) will be reported by the investigator to the sponsor on a separate SAE form within 24 hours. Those SAE which are assessed by sponsor to be Suspected Unexpected Serious Adverse Reactions are further reported via a CIOMS form to the European Medicines Agency (EudraVigilance database) within their specified time frames.

While the study is ongoing, a Development Safety Update Report (DSUR) will be reported annually to the MPA by the sponsor. A monitor from the CTO at CKC, Cancer Theme, Karolinska University Hospital will be responsible for coordinating the monitoring activities of the study and ensure adherence to ICH-GCP guidelines. Authorised representatives for the sponsor and Competent Authorities may carry out audits or inspections at the study site, including source data verification. The investigator must ensure that all source documents are available for audits and inspections.

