	To investigate the effect of GnRHa on ovarian blood supply.
	To estimate the proportion of females with or without GnRHa that develop amenorrhoea (no menstruations).
	To investigate fertility and childbirth after cancer treatment in women with or without GnRHa who attempt pregnancy during follow-up.
	To determine health-related quality of life (QoL) with or without GnRHa during chemotherapy and after cancer treatment.
	To study development of comorbidities during follow-up and bone mineral density after completion of cancer treatment with or without GnRHa.
	To estimate disease-specific oncologic outcomes, recurrence rate, overall survival and disease-free survival with or without GnRHa.

GnRHa, gonadotropin-releasing hormone agonists.

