### Study interventions

At the screening/baseline visit, the principal investigator at each site will ensure that each subject will be provided with written and oral information about the study. The informed consent form is signed before any study-related activities are carried out. A physical examination and complete medical history including demographic data will be performed before start of study treatment. Information regarding concomitant medications including ongoing fertility preservation measures, use of contraceptives and hormonal treatments will be collected at screening/baseline visit and changes in concomitant medications will be assessed throughout the study. Any reported changes will be recorded in the eCRF. Blood samples for measurement of routine blood parameters (a complete blood count, including B-hemoglobulin, white blood cells, differential count and platelets, liver status (alkaline phosphatase), alanine transaminase, aspartate aminotransferase, billirubin and gamma-glutamyl transferase), renal status (sodium, potassium, calcium, creatinine and albumin)) will be collected at baseline and EoT and research blood samples (hormonal markers: AMH, FSH, inhibin, estradiol and LH) and a transvaginal ultrasound (AFC and ovarian blood flow) will be offered at each study visit.

Reproductive outcome data, reproductive health, sexual health and quality of life will be collected through validated questionaires including EORTC QLQ C30, Hospital Anxiety and Depression Scale (HAD) and Female Sexual Function Index (FSFI) .

A full list of study procedures and interventions at each study visit is available in table 3 and in the full protocol (online supplemental material 1).

**Table 3 T3:** Study visits and study procedures

Procedure	Visit 1 Screening baseline	Visit 2 Day 0 (−14/±7 days) Initiation of study treatment (triptorelin/placebo)/ gonadotoxic treatment	Treatment visits during gonadotoxic treatment (triptorelin/placebo) (0–4 additional visits for study treatment) (±7 days)	Visit 3 EoT (±1 month) End of gonadotoxic treatment (1 or 3 months after last administration of triptorelin/placebo)	Visit 4 6 months (±1 months) From EoT	Visit 5–9 1,2,3,4,5 years (±1 months) From EoT
Inclusion/exclusion criteria	X	X				
Informed consent	X					
Fertility preservation	X					
Demography	X					
Physical examination	X					
Vital signs	X	X	X	X	X	X
Medical history	X					
Randomisation		X				
Safety blood samples*	X			X		

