Pregnancy test (if older than 16 and sexually active)	X					
Biochemical markers†	X			X	X	X
Bone mineral density	X			X		X‡
Ultrasound§	X			X	X	X
Study treatment¶		X	X			
Questionnaire (baseline)	X					
Questionnaire (follow-up)				X	X	X
Concomitant medication	X	X	X	X	X	X
Adverse events (AE and SAE)		X	X	X	X	X

*Safety blood samples taken as clinical routine during the cancer treatment are recorded in the eCRF. Safety blood samples at baseline and EoT will be assessed as part of the study.

†Research samples including AMH, follicle stimulating hormone (FSH), inhibin, estradiol and LH.

‡Only at years 1 and 5 of follow-up.

§Antral follicle counts and ovarian Doppler flow.

¶Subjects randomised to treatment GnRHa will receive intramuscular injection(s) of triptorelin, 3.75 mg/month or 11.25 mg/3 months covering the duration of the gonadotoxic chemotherapy, subjects randomised to placebo will receive intramuscular injection(s) of placebo (NaCl 0.9%).

AE, adverse events; AMH, anti-Müllerian hormone; eCRF, electronic Case Report Form; EoT, end of treatment; GnRHa, gonadotropin-releasing hormone agonists ; LH, luteinising hormone; SAE, serious adverse events.

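### The adverse event rules conflict on scope and end date: product-related events to 90 days after the last dose, all events during the study, or events at every visit to year 5

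*Protocol article*

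**What the plan says.** Three statements in the Protocol article bear on which adverse events are collected and for how long.

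- Safety and adverse events, first rule: at each visit, "adverse events (AE) related to the study product are registered, starting at study randomisation and up to 90 days after the last dose".
- Safety and adverse events, the sentence that follows: "All AE that occur during the study and which are observed by the investigator/study nurse or reported by the subject will be registered". Each entry is to carry "complete information regarding seriousness (mild, moderate and severe), intensity and causality".
- Study interventions, Table 3: the row that begins "Adverse events (AE and SAE" is marked at visit 2, at the treatment visits, at visit 3 (EoT), at visit 4 (6 months) and in the last column, "Visit 5–9 1,2,3,4,5 years (±1 months) From EoT".

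Two further entries fix the calendar. Table 3 places EoT "1 or 3 months after last administration of triptorelin/placebo". The section End of study runs the study until the final participant has completed her last follow-up visit, so for each participant follow-up extends to year 5 after EoT.

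**The concern.** The statements disagree on two things that define a safety dataset: which events enter it, and when collection stops. The study has 19 sites, and a reader of this text could follow any of the three rules in good faith.

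Scope matters more for the statistics. Under a related-only rule, an event enters the data only if someone judges it to be linked to a blinded product that is either triptorelin or saline. That judgement is made after randomisation, against the toxicity of chemotherapy. A count filtered in this way is not a count of events by arm. Events that nobody suspects are lost. If the readiness to attribute differs between arms, the comparison shifts even where the true event rates are equal.

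The end date matters because Table 3 asks for AE collection at visits that one of the rules puts out of range, and the article does not say what those visits are meant to capture.

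A smaller defect sits in the same section. Seriousness is given the categories mild, moderate and severe. Those are grades of intensity, and intensity is then listed as a separate item.

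**Working it through.** The article states no figure for this point, so the check sets the rules side by side and then compares their dates.

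**The rules**

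| Source | Scope | End of collection |
|---|---|---|
| Safety and adverse events, first rule | Related to study product only | 90 days after last dose |
| Safety and adverse events, next sentence | All, with causality recorded | End of study (year 5 after EoT) |
| Table 3, AE row | AE and SAE, no causality limit | Year 5 visit |

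The second and third can be read together. The first agrees with neither on scope or on end date.

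**The dates**, counted in days from the last dose, with 1 month = 30.44 days:

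- EoT on schedule: 1 × 30.44 ≈ day 30, or 3 × 30.44 ≈ day 91.
- The 90-day window therefore closes 90 − 30 = 60 days after EoT (gap of 1 month), or 90 − 91 = −1, which is about at EoT (gap of 3 months).
- Earliest visit 4 is EoT + 5 months (6 months less the 1-month tolerance): (1 + 5) × 30.44 ≈ day 183, or (3 + 5) × 30.44 ≈ day 244.
- Visit 9 on schedule is EoT + 60 months: 61 × 30.44 ≈ day 1857, or 63 × 30.44 ≈ day 1918.
- Most favourable case for the window: the 1-month gap shrinks to zero through the EoT tolerance, and visit 4 is counted from there. Then 5 × 30.44 ≈ day 152, still past day 90.

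All six follow-up visits, 4 to 9, thus fall after the 90-day window has closed, although Table 3 marks AE collection at each. The first rule also conflicts with its own opening, which applies it to every study visit.

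**What a related-only filter would do.** Suppose the expected number of events, E, is the same in both arms, and that fractions a (triptorelin) and b (placebo) are judged related. The registered counts are E × a and E × b, so their ratio is a/b whatever E is. The article gives neither fraction. As assumed values only:

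- 50% v 50% gives a ratio of 1.0.
- 60% v 40% gives 1.5.
- 70% v 30% gives 2.3.

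Equal attribution leaves the ratio undistorted, though half the events in that example would still go unrecorded. Under an all-AE rule no such filter applies.

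**The case against.** The strongest reply is that the article only summarises a full protocol, version 2.5, from which sites would work. That protocol is not shown and may hold one clear rule. This stands as a limit: the article does not show that sites will in fact collect differently. It does not remove the point, because the article makes conflicting statements rather than leaving a detail out.

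A second reply is that the first sentence sets the window, the next only says how to record an event, and the later visits are for serious events. But the second sentence covers all AEs and asks for causality, which has little use as a field if only related events are entered, and the Table 3 row names both AE and SAE. Visit 4 could still pick up, in retrospect, events from the days between EoT and day 90. That would not explain visits 5 to 9.

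Three stronger readings are tempting and are not supported:

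- *The safety comparison is made to depend on guessed allocation.* This could arise only if the related-only sentence governs. The section Blinding keeps investigators, site staff and participants blinded, apart from those who prepare the injections, and nothing in the article says that staff work out the arm from symptoms.
- *A spurious significant difference is to be expected.* Any p-value would rest on invented attribution rates and on a between-arm AE test that the article does not specify.
- *The comorbidity objective has no data source.* Table 2 does include the aim "To study development of comorbidities during follow-up", and medical history is taken at baseline only. But Table 3 keeps follow-up questionnaires, concomitant medication and vital signs at every follow-up visit, and bone mineral density at years 1 and 5.

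It is also fair to say that the seriousness wording may be a misplaced parenthesis. Serious events have their own form and a 24-hour limit, and nothing shows that this reporting is affected.

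**Conclusion.** The contradiction stands. The section Safety and adverse events and Table 3 give different scopes and different end dates for AE collection, no text ranks them, and all six visits from 6 months to 5 years lie beyond the 90-day limit. This conclusion needs only the article's own wording and its visit schedule, and it holds under the visit tolerances.

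The effect on the safety comparison is conditional. If the related-only sentence were followed, entry to the data would rest on a causality judgement made after randomisation, and the comparison could be biased by an amount that depends on attribution in each arm, which the documents do not quantify. If the all-AE sentence governs, that concern falls away and what remains is a wording conflict to correct. The seriousness wording is a separate, minor error. The passages should be reconciled, since events left unregistered during treatment may be hard to recover later.

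**What to change.** - Replace the two sentences with one rule: register AEs irrespective of causality, from randomisation to one stated end date, with relatedness recorded as an attribute of each event. Related events can then still be tabulated separately.
- State what is collected at the 6-month to 5-year visits, and mark Table 3 to match, with separate rows for AEs and SAEs if their windows differ.
- Record seriousness as yes/no, and keep mild, moderate and severe for intensity.
- If the full protocol already holds a single rule, correct the article to agree with it.

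The cost is protocol wording, eCRF field definitions and some extra AE entry during chemotherapy. How much extra entry depends on which rule sites now follow, which the article does not show. Randomisation, sample size and the primary analysis are untouched.

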### Patient and public involvement

Patients, patient relatives and patient associations took part in the study design. A patient representative from the Swedish network for Young Women with Breast Cancer acts as a designated consultant for this study. Patient involvement will be continued throughout the study, with the aim to informing on, discuss and improve all aspects of the project, according to the framework suggested by INVOLVE (http://www.invo.org.uk).

## Ethics, permits and dissemination

This study is designed and shall be implemented, executed and reported in accordance with the study protocol, principles of the International Conference on Harmonisation Tripartite Guideline for Good Clinical Practice (ICH-GCP E6 (R2)), applicable local regulations (ie, European Directive 2001/20/EC) and the ethical principles of the Guidelines of the World Medical Association (WMA) Declaration of Helsinki (as amended by the 64th WMA General Assembly, Fortaleza, Brazil, October 2013). The National Institutional review board in Sweden (Etikprövningsmyndigheten, dnr: 2021-03379, approval date 12 October 2021 (approved amendments 12 June 2022, dnr: 2022-02924-02 and 2022-12-13, dnr: 2022-05565-02). Approval by the Swedish Medical Product Agency (Läkemedelsverket) 19 January 2022, Dnr: 5.1- 2021-98927 (approved amendment 4 February 2022). Manufacturing authorisation for authorised medicinal products approved 6 December 2021, Dnr: 6.2.1-2020-079580. Biobankpermit from Stockholm Medical Biobank (SMB) approved 22 June 2022, RBC dnr: 202 253. No substantial changes to the study protocol can be made without renewed approval from the Swedish Ethical Review Authority or the Swedish Medical Product Agency. Changes affecting the study subjects will be reflected in the informed consent form.

Within 6 months of study completion (due to study involving teenagers), the results shall be analysed, a clinical study report with individual data shall be prepared and the study results shall also be reported in the EudraCT database. Study results will be published in open access peer reviewed scientific journals.
